**AIMS OF THE RESEARCH**

- To test the efficacy and acceptability of a new emotional and social mind group training programme for bulimia nervosa (BN) versus a standard cognitive behavioural group therapy programme.
- To explore processes and predictors of outcome in these treatments.
- Specifically, to explore the value of targeting directly difficulties in processing and managing emotion, particularly shame and difficulties in social reasoning, on bulimic symptomatology and self-esteem.

**BACKGROUND**

**The Problem**

Bulimia nervosa (BN) is an eating disorder consisting of recurrent episodes of binge eating followed by compensatory behaviours such as fasting, excessive exercise, or purging, in the context of a general negative evaluation of the self with a specific focus on weight and shape and intolerance of affect. Four to seven percent of young females suffer from full or partial bulimia nervosa (BN) (Hoek *and* van Hoeken, 2003). Typically, BN develops in adolescence and is associated with numerous physical complications and with psychological difficulties, notably anxiety, depression and low self-esteem (see Cooper, 2003, for an overview). Shame is one of the more complex emotions associated with this disorder which can act as a barrier to treatment seeking and engagement (Goss and Gilbert, 2002). Quality of life is poor for sufferers (de la Rie *et al.*, 2005) and the burden on families is high (Perkins *et al*., 2004; Winn *et al*., 2004; 2007). Women with BN who have children may find it hard to feed them and interact with them appropriately (Stein *et al*. 2001**).** Thus BN has a significant cost to sufferers, their families and their offspring.

**Treatment of BN: The Status Quo.**

Over 80 randomised controlled trials have been conducted into the psychological and pharmacological treatment of BN. This research evidence has been summarised in several high quality systematic reviews (National Institute of Health and Clinical Excellence, 2004; Hay *et al.,* 2004). The National Institute of Health and Clinical Excellence (NICE) guidelines (2004) recommend a specific form of cognitive behavioural therapy (CBT-BN) designed by Fairburn and colleagues in Oxford (Fairburn, 1981; Fairburn *et al.*, 1993) to address weight and shape concerns as the first line treatment for this disorder. The recommended treatment dose is 16 to 20 sessions. Individual and group formats of this treatment have been tested, with comparable efficacy (Chen *et al*., 2003). However, with this treatment only approximately 30 to 40 % of people are symptom free at the end of treatment (e.g. Agras *et al*., 2000). The Oxford group have recently updated their CBT treatment to address a broader range of putative maintaining factors (Fairburn *et al*., 2003). However a large RCT (n=154 patients) comparing the more focused (old) version of CBT-BN with the broader (new) version failed to show any difference in outcome (Fairburn, 2007). Thus, there remains an urgent need to develop better treatments for this condition.

**Exploring New Targets for Treatment of BN**

One possibility is that treatment trials have over-focused on targeting the overt symptoms of BN (bingeing and compensatory behaviours) at the expense of the broader intra- and interpersonal attitudes, affects and behaviours typical of the disorder. These factors may be crucial in influencing treatment outcome and/or leaving individuals prone to relapse (e.g. Agras *et al.*, 2000; Openshaw *et al.*, 2004). In a recent systematic review which explored factors predicting poor outcome in eating disorders, two key factors emerged for BN: poor social/interpersonal functioning and negative self-evaluation (Jacobi, 2007). Below we review what is known about these two areas in relation to BN and how this might translate into a new approach to treatment.

*Social/interpersonal functioning and social cognition in BN:*

There is substantial evidence to suggest that women with BN experience difficulties in the social domain during childhood (Troop and Bifulco, 2002; Fairburn *et al*., 1997). Typically they are shy, compare themselves negatively with others and have few friends. Severe life events and chronic difficulties in the social/interpersonal domain trigger the onset of BN in the majority of cases (Schmidt *et al*., 1997; Welch *et al*., 1997).

Women with established BN compare themselves unfavourably to other women and perceive themselves to have a lower social rank than others (Troop *et al*., 2003; Morrison *et al*., 2003). Moreover, they have a more limited social network with fewer supportive relationships (Tiller *et al*., 1997). Pre-existing social difficulties may be worsened by the effects of bulimic symptoms, such as semi-starvation, bingeing or compensatory behaviours (Schmidt *et al*., 1995).

Despite a wealth of literature demonstrating impairments in the social domain in BN, very little work has been done to date on social cognition in BN. Social cognition has been defined as *“the mental operations underlying social interactions, which include the human ability to perceive the intentions and dispositions of others”* (Brothers, 1990). Aspects of social cognition include emotion and social perception, theory of mind and attributional bias. There is some evidence that theory of mind, i.e. the ability to represent the mental states of others in terms of their intentions, desires and beliefs is significantly impaired in patients with BN (Bydlowski *et al*., 2005).

In the treatment literature, Leung *et al*. (2000) found that amongst women treated for BN with group based CBT, it was those who held non-eating disorder-related pathological core beliefs at the outset of treatment who ended up making fewer treatment gains. These included difficulties in the realm of interpersonal functioning and low self-esteem. Thus, there is growing evidence that social functioning and social cognition are impaired in BN and may provide fruitful targets for treatment.

*Negative self-evaluation, shame and social threat*

A consistent finding within the literature concerns the emphasis on affect as a key maintaining factor for BN (Waller *et al.,* 2004). Waller *et al*., (2004) suggest that while anorexia nervosa is characterised by primary avoidance (preventing the experience of distressing cognitions and emotions), BN is characterised by secondary avoidance (removing or blocking the experience of distressing emotions and cognitions). One way of understanding the link between emotion and negative self-evaluation in BN may be through the concept of shame-based self-criticism (Gilbert and Proctor, 2006). In a shame-eliciting situation a person appraises some important aspect of themselves or their behaviour as potentially giving rise to negative appraisal by others and consequently, to a risk of social rejection. Gilbert (2005) hypothesizes that in an attempt to manage this threat of rejection, individuals in a state of shame adopt a mental self-management style characterized by self-criticism, persecution and hostility with the functional intention of prompting behaviour that will reduce rejection threats. Eating disordered individuals have been found to have high levels of both internal shame (self devaluation and self-criticism) and external shame (negative thoughts and feelings about how one exists in the mind of others) (Goss and Gilbert, 2002; Waller *et al*., 1996).

**A New Emotion and Social Mind Training Module**

Taken together the above evidence suggests that negative self-evaluation, poor interpersonal skills, difficulties in understanding the minds of others (the ‘social mind’) and difficulties managing and tolerating emotions, particularly those linked with shame, may be key factors in the maintenance of bulmic symptoms. Based on these ideas we have developed a new emotional and social mind group training program for individuals with BN. We are already using this training module with patients with anorexia nervosa on an individual basis. Preliminary research confirms its utility and acceptability. It is hypothesised that a treatment targeting these factors will lead to positive changes in self-evaluation and interpersonal functioning, and a reduction in bulimic symptoms. Because we know that shame and interpersonal difficulties are central to the pathology of these individuals it is also believed that a group format may provide powerful opportunities to normalise experiences, learn from others and explore the ‘minds’ of others within a safe environment.

**MATERIAL AND METHODS**

**Main hypothesis:**

A 17-session group based intervention (Emotional and social mind training: ESM) targeting the key maintenance variables for bulimia nervosa outlined above will be superior to a 17-session group-based standard CBT programme for this group, in terms of achieving symptomatic improvement in bulimic symptoms and mood.

**Subsidiary hypotheses:**

1. Drop out will be lower in the ESM than the CBT group.
2. Acceptability of treatment will be superior in the ESM group, compared with the CBT programme.
3. ESM will be superior to the CBT programme in terms of the following variables, which will mediate or moderate symptom change:
   1. Reducing intolerance of emotional distress (moderator)
   2. Decreasing negative self-evaluation (mediator)
   3. Increasing adaptive emotional expression and processing (mediator)
   4. Increasing ability to regulate negative mood (mediator)
   5. Reducing self-criticism (mediator)
   6. Reducing negative beliefs about emotions (mediator)
   7. Reducing rumination (mediator)
   8. Reducing socially submissive behaviour (mediator)
   9. Improving social cognition (mediator)

**Design of treatment trial:**

This is a two-arm randomised controlled trial which will evaluate the efficacy of ESM compared to group CBT for adults with BN consecutively referred to the South London and Maudsley NHS Foundation Trust Eating Disorders Service. We will also study processes of and predictors of outcome. Groups will be run by therapists trained in both therapies, and therapists involved will run both groups. Patients in both groups will meet with the research worker to complete the questionnaires and experimental tasks at baseline, at four months, after completing the active treatment, and at six months, after a follow-up period.

**Interventions:**

**Group 1 – Emotional and social mind training (ESM):** Patients in this group will receive a 17-session treatment (4 individual session, 12 group sessions, 1 follow-up session) focusing on the hypothesised maintaining factors outlined above. The individual sessions will be used to develop an individual case formulation. The 12 group sessions will address: identification and understanding of inter- and intrapersonal emotions; the social context of emotions; managing intense and overwhelming emotions; managing shame through compassionate mind training. The follow-up session will be a ‘booster’ for the group. Sessions will take place on a weekly basis. Individual sessions will be 60 and group sessions 90 minutes in length. Group sessions will include eight patients and be facilitated by two therapists. A patient manual for this treatment exists, currently in use within our RCT of individual treatment for patients with anorexia, and can easily be adapted for the group programme.

**Group 2 – Group CBT programme:** Patients in this group will receive a 17-session group-based CBT treatment (4 individual session, 12 group sessions, 1 follow-up session) As with the ESM group, the individual sessions will be used to develop an individual case formulation. The intervention will be based on the group CBT treatment for BN developed by Chen *et al* (2003), adapted from Fairburn *et al* (1993). We chose this programme as the comparison treatment as we wished to match the group format of our ESM intervention whilst comparing it to CBT, the treatment for BN with the strongest evidence base. The timescales and group makeup will be identical to those of the ESM group.

**Outcome measures:**

Research assessments will take place at baseline, 4 months (end of treatment) and 6 months (follow-up).

**Primary outcomes**: Severity of core bulimic symptoms (bingeing, purging, etc…) will be assessed using the Eating Disorders Examination (Fairburn and Cooper, 1993).

**Secondary outcomes:**

Depression, Anxiety and Stress Scale (DASS-21: Lovibond SH and Lovibond PF, 1995); Levels of Self-Criticism Scale (LOSC: Thompson *and* Zuroff, 2004). Distress Tolerance Scale (DTS: Corstophine *et al*., 2007); Beliefs About Emotions Scale (Rimes and Chalder, in preparation); Forms of the Self-Criticizing/Attacking and self-Reassuring Scale (FSCRS: Gilbert *et al*. 2004); Functions of the Self-Criticizing/Attacking Scale (FSCS: Gilbert *et al*. 2004); Submissive Behaviour Scale (SBS: Allan *and* Gilbert, 1997); Rumination Questionnaire (Watkins *and* Barnard, in preparation). Participant satisfaction will be assessed using visual analogue scales. Social cognition tasks: Reading the Mind from the Eyes Test (Baron-Cohen and Hammer (1997); Reading the Mind in Films Task (Golan *et al*., 2006); Interpersonal Perception Task-15 (IPT-15: Costanzo *and* Archer, 1993).

**Randomisation, Blinding and Protection against Bias:**

At the point of referral patients’ suitability for participation will be checked by a clinician. If the patient is suitable and consents, she/he will be introduced to the research assessor who will complete the research assessment. The patient will then be randomised by a computerised system. Stratified randomisation will be used, stratifying for diagnosis (BN or EDNOS) to assign patients to one of the two trial arms. Patients will be told about the outcome of randomisation by the clinician. Throughout the trial every effort will be made to ensure that the assessor remains blind to the treatment condition. All therapeutic sessions will be taped and a random selection of these listened to by the research team to check for adherence to therapeutic model and quality of intervention.

**Inclusion/exclusion criteria:**

Inclusion: patients referred to the SLAM Eating Disorder Service who fully (BN) or partially (EDNOS) fulfil DSM-IV criteria for bulimia nervosa.

Exclusion: insufficient knowledge of English or literacy levels to allow understanding of the intervention materials, active suicidality, severe substance dependence, diabetes or pregnancy. Informed written consent will be sought from patients at initial assessment.

**Proposed sample size:** Because ESM is a novel intervention, power was calculated on the basis of Chen *et al* (2003). A sample size of 30 in each arm of the study will have 80% power to detect a difference in means of -0.850 on the EDEQ Global score assuming that the common standard deviation is 1.15 using a two group t-test with a 0.05 two-sided significance level. Assuming a drop-out rate of 20% a sample size of 76 patients will be needed.

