**STATISTICAL TREATMENT OF RESULTS**

All outcomes will be analysed on an intention to treat basis including all randomised patients. Analyses will also be performed on a ‘per protocol’ basis (including only those who complete treatment) as a sensitivity analyses. Efficacy: We will employ multi-level modelling analyses for missing data using maximum likelihood methods (Everitt, 1998) to compare bulimic symptoms within and between groups. We will control for potential confounding variables (e.g. symptom levels at baseline), by using them as covariates in the analysis. Drop out rates will be compared across the two treatment groups using Pearson’s chi-square test. Predictors and Processes: Regression methods will be used to explore the relationship between potential predictor variables as described above in the hypotheses section and outcomes separately in the two groups. Treatment acceptability: patient satisfaction will be compared across the two treatment groups using t-tests or Mann-Whitney U tests, depending on the distribution.

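### The 80% power makes no allowance for clustering by therapy group, and no planned analysis names therapy group

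*Protocol*

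**What the plan says.** **Delivery.** Under Interventions, each arm has 17 sessions: 4 individual, 12 group and 1 follow-up. For the ESM arm, "Group sessions will include eight patients and be facilitated by two therapists"; the CBT arm is to have the same group composition and timing. The Design section adds that the same therapists run both kinds of group.

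**Sample size** (the paragraph on proposed sample size, under Inclusion/exclusion criteria). The calculation rests on 30 patients per arm, 80% power, a mean difference of 0.85 on the EDEQ Global and an SD of 1.15. The test behind it is described in these words: "using a two group t-test with a 0.05 two-sided significance level". The only inflation is for attrition, at 20%, which brings the total to 76. No ICC, design effect or therapy group is mentioned.

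**Analysis** (Statistical treatment of results). For efficacy, "We will employ multi-level modelling analyses for missing data using maximum likelihood methods", with baseline symptom level among the covariates. The levels of that model are not listed. Drop-out is compared by Pearson's chi-square, and satisfaction by a t-test or Mann-Whitney test.

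**The concern.** Patients who attend the same 12 group sessions share members, facilitators and atmosphere, so their outcomes are likely to be correlated. The protocol's own rationale (the section on the new training module) relies on this: it expects members to learn from one another and have their experiences normalised. With positive correlation, 30 patients in about five groups carry less information than 30 independent patients.

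Two things are at stake. First, the stated power describes a trial without therapy groups. Second, any comparison that leaves therapy group out has a standard error that is too small and a type I error above 5%. With about ten groups in the whole trial, one or two unusual groups could then move the result.

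**Working it through.** **Inputs from the protocol:** difference 0.85, SD 1.15, two-sided alpha 0.05, 30 analysed per arm, 20% drop-out, therapy groups of 8.

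**Assumed, because the documents do not give it:** ICC from 0.01 to 0.10. The number analysed per group, m, is taken as 6 (30 per arm over five groups) to 8 (full groups). Applying 20% drop-out to a group of eight gives 6.4, inside this range.

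**1. The protocol's figure.** Standardised effect = 0.85/1.15 = 0.739. SE = 1.15 × √(2/30) = 0.297. The noncentral t with 58 df gives 80.4% power. For drop-out, 30/0.8 = 37.5, so 38 per arm and 76 in total. Both stated figures reproduce under independence.

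**2. Number of therapy groups.** 38/8 = 4.75, so about five per arm and ten in all. A comparison based on therapy groups has about 10 − 2 = 8 df.

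**3. With clustering.** Design effect DE = 1 + (m − 1) × ICC. SE = 1.15 × √(2 × DE/30). Power comes from the noncentral t with noncentrality 0.85/SE. The type I error of a t-test that ignores therapy group is approximately 2 × P(T58 > 2.00/√DE).

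| ICC | m | DE | Power, 58 df | Power, 8 df | Naive type I error |
|---|---|---|---|---|---|
| 0.01 | 6 | 1.05 | 78% | 69% | 5.6% |
| 0.01 | 8 | 1.07 | 78% | 68% | 5.8% |
| 0.05 | 6 | 1.25 | 71% | 61% | 7.9% |
| 0.05 | 8 | 1.35 | 68% | 58% | 9.0% |
| 0.10 | 6 | 1.50 | 63% | 54% | 10.8% |
| 0.10 | 8 | 1.70 | 58% | 49% | 13.0% |

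Example, ICC 0.05 and m = 6: DE = 1 + 5 × 0.05 = 1.25; SE = 0.297 × √1.25 = 0.332; noncentrality = 0.85/0.332 = 2.56; power 71% on 58 df. A simulation with five groups of six per arm gave a naive type I error of 8.1% at ICC 0.05 and 11.0% at 0.10, in line with the formula.

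**4. Detectable difference.** At ICC 0.05 the difference detectable with 80% power on 58 df is 0.95 (m = 6) to 0.98 (m = 8), against the planned 0.85.

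**5. Baseline adjustment.** With baseline-outcome correlation r and an unchanged ICC, the variance is multiplied by (1 − r²). At ICC 0.05 and an assumed r = 0.5, power is 83% to 80% on 58 df and 74% to 70% on 8 df (m = 6 to 8). To cancel the design effect on 58 df, r must be √(1 − 1/DE), which is 0.45 at DE 1.25 and 0.51 at DE 1.35. The protocol states no r and does not use one in its power calculation.

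**The case against.** A reader might infer that the patients are treated in closed groups, that the whole analysis treats them as independent, and that the trial's standard errors are therefore too small. The protocol does not support that much.

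- **Closed groups.** It gives the size of the group sessions but does not say whether entry is closed or rolling. The point does not need closed groups, since shared sessions and facilitators can induce correlation either way.
- **Efficacy model.** It is multi-level and its levels are not listed. The stated purpose (missing data) suggests visits within patients, but that is an inference. A therapy-group level would contradict nothing in the text, and a statistical analysis plan that is not shown could add it. The type I errors above belong to a naive t-test, which is not the planned efficacy analysis.
- **Therapists.** Because the same therapists run both arms, differences between therapists largely cancel if allocation is balanced. Effects of group membership, and of a therapist being better at one treatment, remain.
- **Size.** The ICC is wholly assumed, and at 0.01 power is still about 78%. The lowest figures combine ICC 0.10 with eight analysed per group, although the protocol's own drop-out rate leaves about 6.4. Baseline adjustment could restore 80% on 58 df.

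All of this stands as a limit on the claim. It does not rescue the power statement, which is fixed in the protocol and assumes independence, or the named tests of drop-out and satisfaction, which ignore therapy group. Baseline adjustment does not correct type I error.

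**Conclusion.** The point holds in a limited form. The 80% power is correct arithmetic for independent patients and makes no allowance for a design delivered in therapy groups. At an assumed ICC of 0.05 without baseline adjustment, power is about 71% to 68% on 58 df and 61% to 58% on 8 df. The true loss may be smaller or larger, because it depends on an ICC and a baseline correlation that the protocol does not state.

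The drop-out and satisfaction comparisons, which test the first two subsidiary hypotheses, are fixed as tests that assume independent patients. For efficacy the conclusion is conditional: standard errors will be too small and type I error above 5% if therapy group is left out of the model. The text does not show that it will be left out, but nothing in it ensures that it will be included.

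**What to change.** Keep 76 patients and make these changes:

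- **Data:** record a therapy-group identifier for every patient from the start; it may be hard to reconstruct later.
- **Efficacy:** name therapy group as a random effect in both arms (visits within patients within therapy groups), with Kenward-Roger or Satterthwaite degrees of freedom because there are only about ten groups.
- **Drop-out and satisfaction:** replace the chi-square and t or Mann-Whitney tests with cluster-aware versions, such as mixed logistic and linear models or another method suited to few clusters.
- **Sample size paragraph:** restate the power with a design effect over a stated ICC range. For example, at ICC 0.05 with 6 analysed per group and no baseline adjustment: about 70% power for 0.85, or 80% for about 0.95, on 58 df, and about 61% for 0.85 on 8 df. If baseline adjustment is counted, state the assumed correlation.

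The cost is some rewording and one extra variable. The downside is a less favourable stated power and somewhat wider intervals. Basing the test on about 8 df lowers power even if the ICC is zero: 71% instead of 80% for 0.85.
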